### Data analysis

The aim of the statistical analysis is the comparison of the main outcome measure (period from extubation to ‘ready for discharge’ from PACU) between the three study groups (intervention groups acupuncture and acupressure and no treatment control). For this variable, an non-normal distribution is assumed. Hence, a nonparametric method, the Kruskal-Wallis test will be applied. *Post hoc* tests will be performed by pairwise comparisons of the three study groups by the Mann-Whitney *U*-test and subsequent Bonferroni adjustment for multiple comparison (*P*-value times three). Primary outcome is defined as the time to discharge from PACU in the press needle acupuncture group in comparison to the no treatment group.

For the secondary target variables, a method according to the distribution of data will be performed. For metric variables, the structure of a normal distribution will be tested by the Kolmogorov-Smirnov test. In case of a normal distribution, a one-way ANOVA will be calculated. Otherwise a nonparametric test for independent observations like the Kruskal-Wallis test will be carried out.

The analysis of categorical data is conducted by the chi-square goodness-of-fit test. The binary case is treated by the chi-square-test of independence.

Data analysis will be performed with the SPSS statistical software system, version 15.0 (SPSS Inc., Chicago, IL, USA) and with SAS/STAT® Software (SAS Institute Inc., Cary, NC, USA). All data entry will be carried out twice.

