### Randomised treatment allocation, blinding and sample-size estimation

Informed consent will be obtained from each participant. Subjects eligible for participation will be randomly assigned to one of the following study groups by using the Internet based randomisation software RANDOULETTE® (Institute of Medical Information Sciences, Biometry and Epidemiology, University of Munich):

• press needle acupuncture: 25 subjects

• no treatment control: 25 subjects

• press plaster acupressure: 25 subjects

Stratification for age will be performed, and an equal distribution between treatment arms (ratio of 1:1:1) will be warranted.

In this trial we will use acupressure (group C) as an intervention to compare acupuncture (group A). Patients and examiners will be blinded for the patients’ assignment to treatment arms A and C. Therefore, we use press needles (0.2 mm × 1.5 mm; Seirin New Pyonex®, Seirin Corp., Shizuoka City, Japan) in group A and non-invasive Seirin press plasters in group C - a device that has successfully been validated for blinding in acupuncture trials [17]. Press plasters do not contain a needle but a blunt knob and are in all other aspects identical to the press needles. According to group allocation, press needles or press plasters will be administered by an independent acupuncturist at the same defined acupuncture points. Instructions regarding point stimulation for subjects and study staff will also be identical. Thereby, patients and examiners will be blinded as laid down in the trial of Myazaki and colleagues who showed that neither patients nor therapists nor examiners know if a sharp tip or a blunt knob is located below the plaster. In contrast to Myazaki, patients will be allowed to stimulate their press device, so that an additional acupressure effect may be elicited, thereby enhancing the overall effects.

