### Sample size calculation

No sample size calculation could be established because at the time of designing the trial there were no parameters available from prior studies. However, we estimated the sample size on the basis of an *a priori* analysis using G*Power (Version 3.1.3, University of Düsseldorf, Germany, see Table 3). We conservatively anticipated the effect size of the tested intervention to be small to medium (d = 0.4, according to Jacob Cohen [21]), which results in a sample size of 66 patients for three study groups. A further adjustment for non-parametric testing and drop outs by 15% results in a total sample size of 75 patients.

**Table 3 T3:** Sample size calculation

F tests:	ANOVA: Fixed effects, omnibus, one-way		
Analysis:	*A priori*: Compute required sample size		
Input:	Effect size f		= 0.4
	α err probability		= 0.05
	Power (1-β err probability)		= 0.8
	Number of groups		= 3
Output:	Noncentrality parameter λ		= 10.5600000
	Critical F		= 3.1428085
	Numerator df		= 2
	Denominator df		= 63
	Total sample size		= 66
	Actual power		= 0.8

A priori analysis as calculated and exported by G*Power (Version 3.1.3, University of Düsseldorf, Germany), anticipating a small to medium effect size f = 0.4, the α-error = 0.05 and the power = 0.8.

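### The test for each metric secondary outcome is chosen from the trial data by an under-specified Kolmogorov-Smirnov pre-test, which at 25 per arm often lets moderately skewed outcomes through to ANOVA

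*Protocol article*

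**What the plan says.** The Data analysis section of the protocol article treats the primary and the secondary outcomes differently.

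- **Primary outcome** (time from extubation to readiness for discharge from the recovery unit). Non-normality is assumed and the test is named in advance: "Hence, a nonparametric method, the Kruskal-Wallis test will be applied".
- **Metric secondary outcomes.** The method depends on the data. First, "For metric variables, the structure of a normal distribution will be tested by the Kolmogorov-Smirnov test". Then, "In case of a normal distribution, a one-way ANOVA will be calculated". Failing that, "Otherwise a nonparametric test for independent observations like the Kruskal-Wallis test will be carried out".

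The section gives no significance level for the pre-test. It does not say whether the critical values allow for an estimated mean and SD. It does not say whether the test is run within each arm, on all patients together or on residuals.

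The trial plans 25 patients in each of three arms (for example "press needle acupuncture: 25 subjects"), and "an equal distribution between treatment arms (ratio of 1:1:1) will be warranted".

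Under Outcome measures, the secondary list includes STAI anxiety (at baseline and twice before induction), intraoperative drug consumption, several emergence times, pain intensity and analgesic consumption. The ward measures are taken six hours after leaving the recovery unit and then three times daily on two days, so up to 1 + 3 × 2 = 7 visits.

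**The concern.** A normality pre-test used as a switch raises two problems in a trial of this size.

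First, failing to reject normality is read as evidence of normality. With few patients the Kolmogorov-Smirnov test is weak, so a skewed outcome can pass and be compared by means, where a few extreme patients carry much weight.

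Second, the method of comparison becomes a function of the outcome data. The same measure can be analysed by ANOVA at one visit and by Kruskal-Wallis at the next without any real change in its shape.

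At stake are the power and consistency of the secondary comparisons. Drug consumption and emergence times are of a kind that may be skewed. The plan already assumes non-normality for one recovery time, the primary outcome, yet sends the secondary emergence times through the pre-test.

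**Working it through.** **The plan's own figure.** The plan gives no figure for the pre-test, so the nearest one to reproduce is the sample size. With f = 0.4, α = 0.05 and three groups, λ = N·f² = 66 × 0.16 = 10.56. The critical F on 2 and 63 degrees of freedom is 3.1428 and the power is 0.818. This agrees with Table 3 of the article (10.56, 3.1428 and 0.8). The plan raises 66 to 75, which is 25 per arm.

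**Inputs for the check**
- From the article: 25 per arm, 75 in total, 1:1:1 allocation, up to seven ward visits.
- Assumed: a 5% level for the pre-test, and the distributions below. The article gives no distribution for any secondary outcome.

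**Statistic.** D = max |Fₙ(x) − Φ((x − x̄)/s)|, with mean and SD estimated from the sample. It is judged in two ways:
- Lilliefors-corrected: critical D is 0.173 at n = 25 and 0.102 at n = 75.
- Uncorrected: 1.358/√n, which is 0.272 and 0.157.

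**Step 1: how often normality is rejected** (20,000 samples per case; Shapiro-Wilk 3,000). The 75 pooled values share one distribution, that is, no treatment effect.

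| Assumed shape (skewness) | Lilliefors, one arm | Uncorrected, one arm | Shapiro-Wilk, one arm | Lilliefors, any of 3 arms | Lilliefors, 75 pooled | Uncorrected, 75 pooled |
|---|---|---|---|---|---|---|
| Gamma, k = 4 (1.0) | 22% | 0.3% | 38% | 53% | 57% | 3.5% |
| Gamma, k = 2 (1.4) | 40% | 1.2% | 67% | 78% | 87% | 18% |
| Lognormal, σ = 0.5 (1.75) | 42% | 1.7% | 64% | 81% | 88% | 24% |
| Exponential (2) | 69% | 5.0% | 93% | 97% | 99.8% | 70% |
| Lognormal, σ = 0.75 (3.3) | 71% | 9.8% | 89% | 97% | 99% | 73% |
| Lognormal, σ = 1 (6.2) | 88% | 27% | 98% | 99.9% | 100% | 97% |

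A rerun with a different random seed gave 21%, 40% and 42% for the first three Lilliefors one-arm figures. Hence the range of about 21 to 42%.

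**Step 2: does one outcome get different tests at different visits?** Seven visits with the same skewness were simulated in 75 patients, with an assumed between-visit correlation of 0.5 or 0.8 (3,000 trials per case). With the Lilliefors form, on pooled data or with any one arm deciding, both ANOVA and Kruskal-Wallis were used within the same outcome in:
- about 86 to 97% of trials at skewness 1;
- about 48 to 80% at skewness 1.4 to 1.75;
- about 1 to 18% at skewness 2, but about 57 to 86% there with the uncorrected form.

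**Step 3: what ANOVA costs when the data are skewed** (25 per arm, 8,000 trials per case; alternative: one arm multiplied by 0.6).

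| Assumed shape | ANOVA type I error | ANOVA power | Kruskal-Wallis power |
|---|---|---|---|
| Gamma, k = 4 | 5.5% | 95% | 95% |
| Lognormal, σ = 0.5 | 4.6% | 92% | 95% |
| Exponential | 4.7% | 34% | 33% |
| Lognormal, σ = 0.75 | 4.3% | 51% | 66% |
| Lognormal, σ = 1 | 3.8% | 24% | 41% |

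The rerun gave 51% against 66% and 24% against 41% in the last two rows, and type I errors of 4.0 to 5.2%.

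**The case against.** A reader might infer that the pre-test has almost no power at this sample size and that clearly skewed outcomes will be sent to ANOVA. The documents do not support that. It needs the uncorrected test, and for the most part testing within each arm, and the article states neither. With the Lilliefors correction, skewness of 2 or more is detected in 69 to 88% of single arms, and almost always when the arms are pooled or any one arm decides. On 75 pooled values even the uncorrected test flags an exponential shape about 70% of the time.

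The harm is also limited. With equal arms ANOVA keeps its type I error, and up to exponential skewness its power is within a few points of Kruskal-Wallis. The marked losses come at heavy skew, where the corrected test usually switches to ranks anyway. The primary outcome is outside the rule, and the article calls the trial a pilot that needs confirmation.

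All of this stands, and it limits the size of the point. One further objection is that the variant, level and testing unit may be set out in a fuller document. That is fair, and their absence is not the fault raised here. The fault is the rule that the article does state, a data-driven switch. Under every variant examined, it passes a substantial share of moderately skewed outcomes or changes test between visits, or both.

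**Conclusion.** The point holds in a limited form. The method for each metric secondary outcome is picked from the trial's own data by a pre-test that, at skewness of about 1 to 1.75, has low to moderate power per arm if corrected (about 21 to 42%). If uncorrected, it has almost none per arm (about 0.3 to 2%) and about 4 to 25% on pooled data. Moderately skewed outcomes can therefore be analysed by ANOVA, and repeated measures of one outcome can be analysed by different tests.

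The consequence is arbitrary test selection, plus a loss of roughly 15 to 17 percentage points of power where a heavily skewed outcome does reach ANOVA (lognormal σ of 0.75 to 1). It is not a false-positive problem.

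These sizes rest on assumed distributions, a 5% pre-test level and, for the visits, assumed correlations. Only secondary outcomes of a pilot are affected.

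**What to change.** Drop the normality test as a decision rule and name the method for each metric secondary outcome before analysis, as the plan already does for the primary outcome:

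- Kruskal-Wallis for drug consumption, emergence times and pain scores, with the same test at every visit.
- ANCOVA adjusted for the baseline value for STAI, whose baseline measurement the plan already collects. This takes that measurement to precede application of the devices, which should be confirmed.
- Any normality check (residual plots, or Shapiro-Wilk if a test is wanted) for description only.

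The change needs a short list in place of the present rule and no extra patients or data. The article reports the trial as ongoing with 50 patients included, so the list could be fixed before analysis. The downside is small: when an outcome really is normal, the asymptotic efficiency of the rank test relative to ANOVA is 3/π = 0.955, a loss of about 5%.

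### The plan names a chi-square goodness-of-fit test for categorical data with more than two categories; read literally, this test does not compare the three arms

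*Protocol article*

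**What the plan says.** The Data analysis section of the protocol article deals with the main outcome first (Kruskal-Wallis, then pairwise Mann-Whitney tests with Bonferroni adjustment). It then turns to the rest: "For the secondary target variables, a method according to the distribution of data will be performed". Metric secondary variables go to a one-way ANOVA or a Kruskal-Wallis test.

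For categorical variables there are two consecutive sentences: "The analysis of categorical data is conducted by the chi-square goodness-of-fit test", followed by "The binary case is treated by the chi-square-test of independence". No reference distribution is given for the goodness-of-fit test, and no other sentence provides a between-arm test for variables with three or more categories.

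The design is a three-arm randomised comparison in which "an equal distribution between treatment arms (ratio of 1:1:1) will be warranted", with 25 patients planned in each arm.

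**The concern.** A goodness-of-fit test answers a one-sample question: does this observed distribution match a distribution fixed in advance? The trial's question is whether the category distribution differs between arms, which is a question of independence or homogeneity in an arm-by-category table.

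An analyst who follows the sentence literally must supply an expected distribution. There are two obvious choices. Pooling the arms and testing against equal shares removes treatment from the analysis. Taking one arm's counts as the expectation treats that arm's sampling error as zero.

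At stake is the interpretation of any secondary variable with more than two categories: a P-value could be reported as a treatment comparison when it is not one, or is one with the wrong error rate.

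**Working it through.** **The plan's own figures.** None is attached to the categorical tests. The only computed figure in the article is the ANOVA sample size. It reproduces (N = 66, f = 0.4, three groups: λ = 66 × 0.4² = 10.56, critical F 3.1428, power 0.818 against a stated 0.8), but it has no bearing on this point.

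**Inputs.** From the article: three arms, 25 per arm, α = 0.05 (stated in the sample size section). Assumed, because the article gives none: three categories, the example counts, and the category shares used in the simulation.

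**Reading 1: pool the arms and test against equal shares.** The expected count is 75/3 = 25 per category, on 2 df.

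- *Nearly identical arms*, 20/3/2, 20/3/2 and 20/4/1, pool to 60/10/5.
  - Goodness of fit: (35² + 15² + 20²)/25 = 1850/25 = 74, P < 0.001.
  - Independence: expected counts per arm are 20, 10/3 and 5/3. The first column contributes 0. In the second and third columns the squared deviations sum to 1/9 + 1/9 + 4/9 = 2/3, giving (2/3)/(10/3) = 0.2 and (2/3)/(5/3) = 0.4. The total is 0.6 on 4 df, P = 0.96.
- *Exactly identical arms*, 15/7/3 three times, pool to 45/21/9.
  - Goodness of fit: (20² + 4² + 16²)/25 = 672/25 = 26.88, P = 0.0000015.
  - Independence: 0, P = 1.00.
- *Clearly different arms*, 15/7/3, 3/8/14 and 7/10/8, pool to 25/25/25.
  - Goodness of fit: 0, P = 1.00.
  - Independence: all expected counts are 25/3 and the squared counts sum to 765, so 765/(25/3) − 75 = 91.8 − 75 = 16.8 on 4 df, P = 0.002.

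**Reading 2: take the control arm's counts as the fixed expectation.** With equal arm sizes, the difference between two arms has twice the variance that the test assumes. In large samples the statistic therefore behaves as 2 × χ² on 2 df under the null. The type I error is P(χ² > 5.991/2) = exp(−5.991/4) = 0.224 for one pairwise comparison.

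**Simulation at the trial's size.** 20,000 runs under the null, 25 per arm, nominal 5%. Rejection rates:

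| Assumed shares | Independence, 3 × 3 | Reading 2, one active arm v control | Reading 2, at least one of two | Reading 1 |
|---|---|---|---|---|
| 1/3, 1/3, 1/3 | 5.1% | 25.9% | 40.7% | 5.3% |
| 0.5, 0.3, 0.2 | 4.9% | 26.6% | 41.6% | 83.6% |
| 0.6, 0.25, 0.15 | 4.7% | 25.9% | 40.8% | 99.7% |

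Runs with an empty control category (5, 69 and 349 of 20,000) were left out of the Reading 2 columns, since the statistic is then undefined. The Reading 1 column depends only on how unequal the overall shares are.

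**The case against.** The best defence is that this is a slip of terminology in a minor part of the plan. The same Pearson statistic underlies both tests, and a statistician analysing a three-arm trial would probably run the contingency-table version anyway. That is plausible, but the text does not support it well: the next sentence names the test of independence separately and limits it to the binary case. Nor is this a detail that a condensed article leaves to a fuller document. The article names a specific test, and that test does not fit the purpose.

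The defence on scope is stronger and largely stands. The primary, metric and binary analyses are untouched. No secondary outcome is expressly designated as having more than two categories. A reader might infer that graded nausea and vomiting is one, but the outcome lists give PONV and shivering as occurrences, which read as yes/no and so fall under the correctly named test. The three-level items in Table 2 (pain, bleeding, consciousness and others) are components of summed recovery scores. They would come under the faulty sentence only if analysed item by item, which the article does not announce.

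It is also fair to say that both readings worked through above need an expected distribution that the article never chooses. The rejection rates show what could happen under literal use; they do not predict what this trial will report. Finally, the Discussion presents the trial as a pilot whose positive result would need confirmation, so no confirmatory claim rests on these variables.

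**Conclusion.** The sentence is wrong as written: it assigns multi-category data a test that does not compare arms and supplies no reference distribution.

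If it is applied literally, the error can go either way, towards rejection with identical arms or towards missing a real difference. With one arm as the fixed expectation and three categories, the type I error per comparison is about 22% asymptotically. At 25 per arm it is about 26% to 27%, and 41% to 42% for at least one of the two active arms. These figures rest on assumed category shares and on a choice of expectation that the article does not make.

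A reader might go further and conclude that multi-category results will be declared significant without any treatment effect, or that the trial's secondary analyses are invalid as a whole. The documents do not support that. It would take a multi-category endpoint, literal execution and a particular expected distribution, none of which the article establishes. Severity is low to moderate.

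**What to change.** Replace the two sentences on categorical data with one stating that all categorical variables, binary or with more categories, are compared between arms by the chi-square test of independence on the arm-by-category table. In the simulation above this test held 4.7% to 5.1% at a nominal 5%.

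Two refinements are optional. One is an exact version for sparse tables: with 25 per arm, a category with an overall share below 20% has an expected count below 25 × 0.20 = 5. The other is a rank test for ordered grades.

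The cost is one sentence. Design, sample size and data collection are unaffected, and the tests are standard procedures in the software the article names. The Trial status section reports the study as ongoing at first submission, so the wording could have been settled before analysis.

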## Discussion

The AcuARP trial investigates the effectiveness of acupuncture on post anaesthetic recovery and its use as an adjunct therapy to improve patient’s recovery in the whole perioperative setting.

Inclusion and exclusion criteria were held pragmatic in order to facilitate screening and recruitment. The chosen trial population is homogeneous and the operations undertaken are common; hence a maximised and improved routine care would be of general interest.

Limitations include the restricted sample size as the trial was planned as a pilot study. In case of a positive study outcome, further confirmatory studies will be needed. In addition, a standardised clinical procurement, using strictly standardised anaesthesia and standardised acupuncture regimen may impede generalizability of the findings.

### Acupressure as a control procedure

The investigators have chosen acupressure as a control procedure in this trial as it provides the possibility of blinding both patients and examiners. Successful patient blinding using the press needle/plaster device has been proven by Miyazaki *et al*. [17]. Examiners will be blinded too, since they do not know if a sharp needle (acupuncture) or a blunt knob (acupressure) is located below the plaster [17].

This special trial design will allow us to assess different needle-specific treatment effects [22]: on the one hand, using a needle tip, acupuncture will be performed by penetrating the skin causing specific physiologic effects. Those may be distinguished from similar physiologic effects caused by acupressure, on the other hand, which can also be a strong stimulus by touching and kneading the skin, but without penetration. Emotional, hormonal and affiliative responses to touch have already been assured [23]. By comparing acupuncture to acupressure, this trial will provide important evidence not only about the importance of the needle stimulus of acupuncture but also about whether acupressure might also bring about a therapeutic benefit in the perioperative setting. This in particular seems to be of interest when taking into account patient populations that are at higher risk of suffering from side effects from local bleeding.

The use of press needles was also chosen for other reasons. Perioperative treatment has to be practicable, applicable, safe and scientifically approved. The practicability will be given, as press needles have only to be fixed once: for this trial after inclusion, feasible in daily routine along with the anaesthesiologic consent. The chosen acupuncture sites are not within the surgical area. Patients can easily access the needles and press them if necessary. Press plasters are water resistant and sustain up to one week. The safety of acupuncture has been described in depth, suggesting that acupuncture is free of severe side effects and being considered a safe intervention [24]. Blunt rather than sharp knobs are even less traumatic. There is a small number of trials dealing with the safety of press needles; one long-term observation over one year in cancer patients suggests a ratio of 10% of minor side effects, mostly rashes [25]. Furthermore, press needles are short (1.7 mm) and needling sites are located in a safe distance from inner organs. Thus, severe adverse events such as pneumothorax or injury of inner organs are avoided. The scientific proof was previously subject to other trials, suggesting that it is worth using acupuncture in the perioperative setting [14,15].

